### Recruitment and Consent

The primary recruitment method for both MM and comparison groups will be through UF’s health care system contact registry (Consent2Share), where patients have consented to be contacted for research. The research team will first contact patients with chronic pain in the contact registry via email or messages within the MyChart patient portal; those who are interested will then be prescreened for preliminary eligibility over the phone. The UF Pain Research and Intervention Center of Excellence (PRICE) registry (IRB201400126) will also be used to recruit participants who have previously consented to be contacted about future research studies.

Additional participant recruitment will take place at various chronic pain, primary care, and MM clinics across the state of Florida, as well as the Veterans Affairs (VA) Medical Center. The research coordinator or staff has a designated space at clinics to determine preliminary eligibility, explain details of the study, and schedule an in-person baseline visit. Clinic staff or clinicians will distribute study flyers and contact forms to their patients and waiting areas. The VA coordinators will also prescreen potential research participants via VA medical records or physician referrals and contact potential participants via mail, email, or phone calls. Clinics may also send electronic versions of IRB-approved flyers and recruitment materials to their scheduled patients or direct patients to fill out an online form to express interest in the study. We will recruit in community settings via flyers in research facilities and clinics and through radio advertising. All assessments will be conducted at research facilities in Gainesville or Jacksonville, Florida.

### Study Design

#### Overview

All participants will complete an in-person screening, including a urine sample to confirm their marijuana use status, verification of musculoskeletal or neuropathic chronic pain using medication bottles or medical records, and a screening questionnaire. Participants will complete in-person assessments at baseline and 12 months, including survey questionnaires, cognitive testing, blood pressure measurement, and biomarker collection (blood samples for cannabis metabolite tests, telomere length, and inflammation/inflammasome markers). After the initial baseline visit, participants will complete technology-based real-time assessments using a smartphone-based EMA app to measure subjective elements of pain intensity, emotional and physical functioning, and sleep. Participants will also be provided with a wearable Fitbit sensor to record objective data on heart rate, physical activity, and sleep. The EMA surveys and Fitbit data will capture real-time short-term effects during the first month and for 1 week every 3 months over 12 months. Biospecimen collection (urine tests and blood samples) and a follow-up survey will be repeated every 3 months. Participants are encouraged to provide feedback regarding study procedures throughout their participation to inform future revisions to the protocol. Figure 1 provides an overview of the study procedures. A detailed timeline for each measure and assessment conducted throughout the course of the study can be found in Table 1.

**Figure 1. F1:**
[figure not shown]
Study procedure overview. EMA: ecological momentary assessment; MM: medical marijuana.

**Table 1. T1:** Summary of study measures and assessments.

Measure	Baseline	3, 6, and 9 months	12 month	Source
Screening				
Presence of tetrahydrocannabinol (THC) in urine	✓	✓^a^	✓^a^	Urine test
Current/history of substance use disorders	✓			DAST-10^b^ [56,57]
Health literacy	✓			REALM-R^c^ [51]
Biometric data/biospecimen				
Height and weight	✓		✓	N/A^d^
Blood pressure	✓	✓	✓	N/A
Telomere length	✓		✓	Blood sample: buffy coat [58-60]
Cannabinoids and metabolites	✓	✓	✓	Blood sample: cannabinoids/metabolites assay [61-63]
Inflammation and neurodegeneration	✓	✓	✓	Blood sample: inflammasome and neurodegeneration biomarker test (exploratory)
Pain sensory tests				
Pain sensitivity	✓		✓	Punctate mechanical stimuli test and pressure pain threshold [64]
NIH^e^ Toolbox Cognition Battery				
Executive function	✓		✓	NIH Toolbox dimensional change card sort test and NIH Toolbox Flanker inhibitory control and attention test [65]
Processing speed	✓		✓	NIH Toolbox pattern comparison processing speed test [65]
Episodic memory	✓		✓	NIH Toolbox picture sequence memory test [65]
Working memory	✓		✓	NIH Toolbox list sorting working memory test [65]
Language	✓			NIH Toolbox picture vocabulary test and NIH Toolbox oral reading recognition test [65]
Other assessments				
Real-time outcomes (pain, mood, sleep) and medication/MM^f^ use	4 wk	1 wk	1 wk	EMA^g^ smartphone app and Fitbit; BSI^h^ [66]

a Urine test at follow-up does not affect eligibility.

b DAST-10: Drug Abuse Screening Test.

c REALM-R: Rapid Estimate of Adult Literacy in Medicine, Revised.

d N/A: not applicable.

e NIH: National Institutes of Health.

f MM: medical marijuana.

g EMA: ecological momentary assessment.

h BSI: Brief Symptom Inventory.

#### Group Assignment

Participants will be assigned to the MM group or the comparison group based on their responses to baseline screening questions regarding current interest or disinterest in starting MM treatment. Group assignment will remain consistent for each participant, regardless of whether they change their mind throughout the course of the study. Participants interested in initiating MM treatment will be given information about local MM physicians who can certify them for a Florida MM card. Additional compensation for delaying MM treatment to enroll in the study will also be provided to participants who begin MM treatment within 4 weeks after their baseline visit to cover most of the cost for MM physician visits and the initial charge to obtain their MM card in Florida.

#### Surveys at Baseline and 3-, 6-, 9-, and 12-Month Follow-Ups

Surveys at all time points take approximately 30 to 45 minutes for participants to complete. The length of the visit can be a barrier for older adults, especially those with chronic pain. In the interest of saving participants’ time and preventing fatigue during the in-person assessment, participants will have the option to complete the survey remotely before their visit. Participants are offered snacks and beverages during in-person visits and can take as many breaks as needed. The survey includes questions such as demographics, health status measured using the Charlson Comorbidity Index and health history [67], medication and supplement use measured using the Medication Quantification Scale, patient-reported medication symptoms adapted for MM, nonpharmacological treatments [68-70], self-rated health, mental well-being, history of and current nonmedical marijuana use, and substance use. Established scales will be used to assess variables such as pain measured by the Brief Pain Inventory, Graded Chronic Pain Scale (GCPS), Patient Global Impression of Change, and Patient-Reported Outcomes Measurement Information System (PROMIS) Pain Interference Scale [71-74]; marijuana use measured by the comprehensive marijuana motives questionnaire adapted by Lankenau et al [75-78], Medical Cannabis Expectancy Questionnaire, and Cannabis Use Disorders Identification Test-Revised; substance use measured by the World Health Organization-Alcohol, Smoking and Substance Involvement Screening Test [79]; quality of life measured by the PROMIS Global-10 [80]; depression and anxiety measured by the PROMIS Anxiety and Depression Scales [81]; social desirability measured by the Marlowe-Crowne Social Desirability Scale [82]; post-traumatic stress disorder measured by the Primary Care-Post-Traumatic Stress Disorder Scale [83]; and sleep quality measured by the Pittsburgh Sleep Quality Index [84]. A full list of core survey assessments can be found in Table 2, and information on how these measures are related to each study aim is outlined in the *Analytical Strategy* section. Participants will complete the survey independently or with assistance from research staff.

**Table 2. T2:** Summary of measures included in the core and quarterly follow-up surveys.

Measure	Baseline	3, 6, and 9 months	12 month	Source
Demographics, income, and insurance	✓			N/A^a^
Medical history	✓	✓	✓	CCI^b^ and health history [67]
Current medication use	✓	✓	✓	MQS^c^ [68]
Marijuana use				
Marijuana use motive	✓			CMMQ^d^—adapted by Lankenau et al [75,78]
MM^e^ attitudes and perceptions	✓		✓	N/A
Positive and negative MM expectations	✓			MCEQ^f^ [76]
Cannabis use disorders	✓		✓	CUDIT-R^g^ [77]
List of MM products^h^		✓	✓	N/A
Recreational marijuana use	✓	✓	✓	N/A
Marijuana-related adverse events		✓	✓	PRMS^i^—adapted for MM^h^ [70]
Pain				
Pain assessment	✓	✓	✓	BPI^j^ [71]
Pain severity	✓		✓	GCPS^k^ [72]
Change in pain			✓	PGIC^l^ [73]
Chronic pain stage	✓		✓	Pain FITT^m^ [37,58,85]
Pain interference	✓	✓	✓	PROMIS^n^ Pain Interference Scale-Version 4a [74]
Nonpharmacological treatments	✓	✓	✓	Nonpharmacological therapies for chronic pain [69]
Emotion				
Depression	✓	✓	✓	PROMIS Depression Scale-8a [81]
Anxiety	✓	✓	✓	PROMIS Anxiety Scale-8a [81]
Health-related quality of life	✓	✓	✓	PROMIS Global-10 [80]
Social desirability	✓			MCSDS^o^ [82]
PTSD^p^	✓			4-item PC-PTSD^q^ Scale [83]
Other				
Sleep	✓	✓	✓	Pittsburgh Sleep Quality Index [84]
Substance use	✓		✓	WHO-ASSIST^r^ [79]

a N/A: not applicable.

b CCI: Charlson Comorbidity Index.

c MQS: Medication Quantification Scale.

d CMMQ: Comprehensive Marijuana Motives Questionnaire.

e MM: medical marijuana.

f MCEQ: Medical Cannabis Expectancy Questionnaire.

g CUDIT-R: Cannabis Use Disorders Identification Test-Revised.

h Administered to the Medical Marijuana group only.

i PRMS: patient-reported medication symptoms.

j BPI: Brief Pain Inventory.

k GCPS: Graded Chronic Pain Scale.

l PGIC: Patient Global Impression of Change.

m Pain FITT: pain frequency, intensity, time, and total number of pain sites.

n PROMIS: Patient-Reported Outcomes Measurement Information System.

o MCSDS: Marlowe-Crowne Social Desirability Scale.

p PTSD: post-traumatic stress disorder.

q PC-PTSD: Primary Care PTSD.

r WHO-ASSIST: World Health Organization-Alcohol, Smoking, and Substance Involvement Screening Test.

Follow-up surveys will be conducted at 3, 6, 9, and 12 months after the baseline assessments. Quarterly follow-up surveys at 3, 6, and 9 months will collect information on MM products (if applicable), current medications, and any health updates. At the 12-month visit, participants will complete the same core survey as the baseline, excluding demographic questions. Follow-up surveys may be completed remotely.

#### Biospecimens

At every visit, participants will be asked to provide a urine sample to test for THC. For remote follow-up visits, a drug test cup will be mailed with instructions on how to upload a photo of the results.

We will also collect approximately 4 mL of blood every 3 months from each participant completing an in-person visit. Plasma will be shipped to the University of Colorado laboratory for analysis of various cannabinoids and associated metabolites (6a-OH-CBD, 7-OH-CBD, 11OH-THC, THC, CBD, CBC, CBD-gluc, THC-gluc, 7-CBD-COOH, THC-COOH, THC-COOH-Gluc, CBN, CBG, THCV, CBDV) [61-63]. Backup plasma samples may also be shipped to the University of Miami for inflammasome and/or neurodegeneration biomarker tests for exploratory analysis.

For the blood drawn at baseline and 12-month visits, the buffy coat will be frozen for analysis of telomere length, a biological measure of cellular aging [58-60]. Collected samples will be sent to the [name] Lab at the University of California, San Francisco, for analysis at the end of the study.

#### Anthropometric and Cardiovascular Assessments

Participant’s height and weight will be measured at the baseline and 12-month study visits. Every 3 months, study staff will measure the participant’s blood pressure using a vital sign monitoring device during in-person visits.

#### Clinical and Experimental Pain Measures at Baseline and 12-Month Visits

Clinical pain measures will include the GCPS [72], which assesses chronic pain severity, and the Chronic Pain Stage, which is a stage measure based on pain frequency, intensity, time, and total number of pain sites [37,58,85]. Experimental pain measures will include punctate mechanical stimuli and pressure pain threshold to assess pain sensitivity, which has shown predictive utility for pain severity in chronic pain patients [64].

#### Standardized Neurocognitive Assessments at Baseline and 12-Month Visits

After completing the baseline and 12-month follow-up surveys, participants will complete cognitive assessments using the NIH Toolbox Cognition Battery, a standardized neurocognitive assessment tool available as an iPad app [65]. It contains 7 cognition battery tests assessing 5 cognitive subdomains: Language, Executive Function, Episodic Memory, Processing Speed, and Working Memory [65]. Table 1 shows the full list of assessments used. Three composite scores are created from these tests (Fluid, Crystallized, Total Composites), with normative standards available for comparison [86,87]. At the 12-month follow-up visit, only the fluid composite score will be used.

#### EMA Survey

Participants starting MM treatment will complete a 1-week EMA using a smartphone app (mEMA, illumivu Inc. or MetricWire) before they start MM and a 3-week EMA after they begin using it. They will also complete a 1-week EMA at 3, 6, 9, and 12 months to track their MM use and longitudinal real-time outcomes. The comparison group will complete an approximately 4-week EMA at baseline and an approximately 1-week EMA at 3, 6, 9, and 12 months to answer questions regarding medication and nonpharmaceutical use.

This study will use 4 random prompts (roughly 1 every 4 hours) to assess real-time pain levels, mood (measured by the Brief Symptom Inventory[66]), and other symptoms (eg, nausea, sleepiness, dizziness) and 1 daily prompt to assess overall pain levels in the past 24 hours, the previous night’s sleep quality, and medications taken in the past 24 hours besides MM. After the baseline survey and cognitive assessment, study staff will train participants on how to use the EMA with practice questions. Participants starting MM will also be asked to upload a picture of the label on the MM products they have been using to validate the product information.

#### Fitbit Activity Tracker

Participants will also wear a Fitbit Charge 5 or 6 (the latest model available) in parallel with EMA for objective measures of physical activity, heart rate, and sleep duration and quality. Data will be accessed via Fitabase, a service that allows centralized management of Fitbit data.

#### Quality Assurance

The research team will not be permitted to recruit participants or conduct visits until they receive training and pass evaluation by the study coordinators or principal investigator (PI). EMA and Fitbit data will be assessed multiple times per week to monitor for any missing data or issues with participant compliance. Weekly meetings with the research team and biweekly meetings with the investigators will be held to discuss any protocol deviations or discrepancies. The research coordinators and data manager will conduct biweekly checks of all survey data and visit log notes for discrepancies.

### Analytical Strategy

#### Power and Sample Size

The total sample size was calculated based on Aims 1 and 2, for which statistical analysis will use a “difference-in-differences” approach. Power was calculated to ensure the detection of differences between the baseline and 12-month follow-up survey in Aim 2, which requires a larger sample size than the intensive longitudinal data from EMA assessments. Assuming a 3:1 ratio of MM versus comparison group and within-subject correlation of variables of 0.5, the sample size required to detect an effect size of 0.3 SD between-group difference (small to medium effect size) [88] in the outcome measured by standardized scales (eg, reduction in pain intensity measured by GCPS), with 80% power (type I error=0.05), is 352 (264 vs 88). Assuming 20% attrition, based on our pilot study (79% retention without a preplanned 12-month follow-up), the final sample size required to achieve the power is 440 (330 vs 110) [89]. For Aim 1, we will have more than 80% power to detect an effect size of 0.3 SD in between-group difference because there will be more repeated measurements in Aim 1. For Aim 3, we will have 264 participants for the analysis since only the MM group will be analyzed. After adjusting for multiple testing with the conservative Bonferroni method [90], the adjusted type I error rate becomes 0.05/7=0.007, under which we will have 99% power to detect the Pearson correlation of 0.3.

#### Aim 1

Aim 1 is to determine whether MM use leads to short-term changes in pain intensity and physical and emotional functioning, as measured in real time by EMA (subjective data) and the Fitbit device (objective data).

Key outcomes of interest include pain intensity, physical functioning, emotional functioning, and sleep. Pain intensity will be assessed from the EMA surveys using self-reported real-time pain intensity on a 0 to 100 visual analog scale. Physical functioning will be assessed from the EMA surveys using self-reported real-time pain interference and from the Fitbit using step counts. Emotional functioning will be assessed from the EMA surveys using self-reported real-time anxiety and depression symptoms (Brief Symptom Inventory).

Separate generalized linear mixed-effects models (GLMM) or generalized estimating equations (GEE) will be used to compare the temporal changes in each of the main outcomes (pain intensity level, physical and emotional functioning) between the MM and comparison groups. A difference-in-difference analysis will be conducted. A propensity score method will account for potential baseline differences between the 2 groups for analysis with inverse probability of treatment weighting. Daily MM use measured via EMA will be a time-varying exposure variable in the GLMM or GEE models to account for crossover between groups. The research team will also include time-varying covariates in these models to account for potential impacts of other non-pharmaceutical pain treatments (eg, category of treatments and number of sessions for each category) and non-MM use (self-reported frequency/quantity).

#### Aim 2

Aim 2 is to evaluate whether MM use leads to longer-term changes over a 12-month period based on self-reported pain intensity, emotional and physical functioning, health-related quality of life, and cellular aging markers such as telomere length.

Key outcomes of interest include pain intensity and interference, physical functioning, emotional functioning, cognitive function, opioid, benzodiazepine, and other medication use, sleep quality, quality of life, and cellular aging. Pain intensity will be assessed from EMA surveys, similar to Aim 1, as well as Brief Pain Inventory and GCPS responses from the core survey. Physical functioning will be assessed from EMA surveys, similar to Aim 1, and the PROMIS Pain Interference Scale from the core survey. Emotional functioning will be assessed from EMA surveys, similar to Aim 1, and the PROMIS Anxiety and Depression Scales from the core survey. Cognitive function will be assessed using the NIH Toolbox Cognition Battery and self-reported changes in cognition from the core survey. Opioid, benzodiazepine, and other medication use will be assessed using the Medication Quantification Scale from the core survey. Sleep quality will be assessed using self-reported sleep duration and quality from the EMA surveys, the Pittsburgh Sleep Quality Index from the core survey, and Fitbit-recorded sleep duration. Quality of life will be assessed using the PROMIS Global-10 and Patient Global Impression of Change from the core survey. Cellular aging will be assessed by measuring telomere length from buffy coat samples.

The research team will analyze 2 types of data: (1) intensive longitudinal data (EMA, Fitbit, opioid, and benzodiazepine dose) and (2) data collected only at baseline and 12 months (core survey, cognitive tests, biomarkers). For intensive longitudinal data, separate GLMM or GEE models will be built to compare longitudinal trajectories in each outcome (pain intensity, emotional and physical functioning, opioid dose) measured at multiple time points over 12 months between the MM group and the comparison group. As in Aim 1, we will treat MM use as a time-varying exposure variable to account for crossover and include other nonpharmaceutical pain treatments and nonmedical marijuana as time-varying covariates. The analysis will use the exact time (eg, hours) of each measurement (instead of days) for constructing the trajectory and thus does not need to average measurements within each day into a single value. For measures collected only at baseline and 12 months, generalized linear regression models will be used to compare group differences in the survey data (eg, anxiety/depression, disability, quality of life), cognitive test results, and telomere length. Additionally, milligram morphine equivalent opioid dosage from the prescription drug monitoring program will be obtained through medical records to assess differences in the risk of unintentional overdose between the MM and comparison groups.

#### Aim 3

Aim 3 is to examine among individuals initiating MM which MM product characteristics (ie, THC:CBD ratio, administration route, dose) are associated with greater improvements in the outcomes defined in Aims 1 and 2, or with a greater incidence of side effects, and explore whether individual differences (eg, sex, baseline pain phenotype) moderate these relationships. Key outcomes of interest are defined in Aims 1 and 2.

Separate GLMM or GEE models using each product characteristic as a predictor will be developed. As in Aims 1 and 2, we will treat MM use as a time-varying exposure variable to account for crossover and include other nonpharmaceutical pain treatments and nonmedical marijuana as time-varying covariates. The research team will construct a multivariate model to include all 3 product characteristics (ie, THC:CBD ratio, administration route, dose) as predictors for each main outcome using stepwise model selection or least absolute shrinkage and selection operator to account for potential interactions within these product characteristics. To determine significant moderating effects of interpersonal differences, separate GLMM or GEE models will be conducted by gender (male vs female) or at each level of the moderator (low/moderate/high stage of pain, low/high marijuana expectancy, low/high social desirability bias) to assess whether the main effect of the MM product characteristic on each main outcome differs by group membership or the level of the moderator.

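### The stated 352 (264 vs 88) is not the sample size for the named difference-in-differences analysis: an unweighted change-score contrast with the article's own inputs needs 468, and has about 68% power at 264 vs 88.

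*Protocol article*

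**What the plan says.** All of the sizing is in the Protocol article, Power and Sample Size.

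- Design: "The total sample size was calculated based on Aims 1 and 2, for which statistical analysis will use a “difference-in-differences” approach".
- Contrast that drives the number: "Power was calculated to ensure the detection of differences between the baseline and 12-month follow-up survey in Aim 2".
- Inputs: "Assuming a 3:1 ratio of MM versus comparison group and within-subject correlation of variables of 0.5", and "an effect size of 0.3 SD between-group difference (small to medium effect size").
- Result: the number required "with 80% power (type I error=0.05), is 352 (264 vs 88").
- Attrition: "Assuming 20% attrition, based on our pilot study (79% retention without a preplanned 12-month follow-up"), so that "the final sample size required to achieve the power is 440 (330 vs 110").

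The Aim 1 section repeats the method ("A difference-in-difference analysis will be conducted") and adds a propensity score with inverse probability of treatment weighting. The Aim 2 section says that outcomes measured only at baseline and 12 months are compared between groups by generalized linear regression. It does not say whether the baseline value of the outcome is a covariate.

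**The concern.** The section prints the method, every input except sidedness, and the output, so the output can be checked. A difference-in-differences between two time points compares mean changes. Its variance therefore depends on the within-subject correlation through 2(1 − ρ), and at ρ = 0.5 this removes none of the outcome variance. The printed number implies that a quarter of the variance has been removed.

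This is the only derivation behind 440. If the 12-month result is null under the named analysis, a reader would take it as 80%-powered evidence against a 0.3 SD effect. The real type II error for the unweighted contrast would be about 32%, not 20%. Groups are also formed by participants' interest in starting treatment (Group Assignment section), not by randomisation. If baselines differ, difference-in-differences and baseline adjustment can estimate different quantities, so which one the study is sized for is more than a question of precision.

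**Working it through.** **Inputs (Power and Sample Size).** Difference 0.3 SD; ratio 3:1; ρ = 0.5; power 80%; type I error 0.05, taken as two-sided because the article does not say. Let f be the variance of the analysed quantity in units of the outcome variance.

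**Formula.** Comparison-group size n = (1.960 + 0.8416)² × f × (1 + 1/3) / 0.3² = 7.849 × 1.3333 / 0.09 × f = 116.28 × f.

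**1. Reproducing the printed figure.** With f = 0.75, n = 87.21, rounded up to 88; 3 × 88 = 264; total 352. This is exact. At ρ = 0.5 the factor 0.75 arises in two ways:
- baseline-adjusted follow-up (ANCOVA): 1 − ρ² = 1 − 0.25 = 0.75;
- group difference averaged over the two time points: (1 + ρ)/2 = 0.75. This one does not estimate change.

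**2. The named analysis.** For the change score, f = 2(1 − ρ) = 1.0. Then n = 116.28, rounded up to 117; 3 × 117 = 351; total 468. A t-based calculation also gives 468.

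**3. Power at 264 vs 88.** 1/264 + 1/88 = 0.015152.
- f = 1.0: SE = √0.015152 = 0.1231; 0.3/0.1231 − 1.960 = 0.477; power 68.3%. The noncentral t gives 68.1% and a simulation of 20,000 runs gives 68.0%.
- f = 0.75: SE = 0.1066; 0.3/0.1066 − 1.960 = 0.854; power 80.4%.

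**4. Detectable difference at 80% power, f = 1.0.** 2.8016 × 0.1231 = 0.345 SD.

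**5. Other readings of the text.**

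| Reading | Total at 3:1 | Power at 264 vs 88 |
|---|---|---|
| Change score, two-sided | 468 | 68.3% |
| 0.3 read as SD of the change | 468 (at ρ = 0.5 the two SDs are equal) | 68.3% |
| 12-month value only | 468 | 68.3% |
| Change score, one-sided 0.05 | 92 + 276 = 368 | 78.6% |
| Factor 0.75, two-sided | 352 | 80.4% |

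A 1:1 two-sample t-test with variance 1.0 needs 176 per group, also 352 in total, but it ignores the stated 3:1 ratio. The article does not show which route was used.

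**6. Correlation that would rescue the figure.** 80% power at 264 vs 88 needs 2(1 − ρ) = 0.09/(7.849 × 0.015152) = 0.757, so ρ = 0.622 rather than 0.5.

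**7. Attrition and enrolment.** 352/0.8 = 440, so that step is right. If all 440 were evaluable (330 vs 110), change-score power would be 77.8%. Enrolment in October 2025 (277 and 122, Results section), less 20%, is about 222 and 98: SE = √(1/221.6 + 1/97.6) = 0.1215, and power is about 69%.

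**The case against.** **352 is not a slip.** It is exact for a baseline-adjusted analysis, and the Aim 2 regression could be one. An article may leave its covariate list to the analysis plan. This stands in part: it shows that the fault is a mismatch between the named analysis and the variance used, and it opens an easy remedy. It does not rescue the text, because the sizing paragraph explicitly names difference-in-differences for Aim 2 and the regression paragraph names no baseline adjustment.

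**Difference-in-differences need not mean a raw change-score comparison.** If the propensity model contained the baseline outcome, weighting could recover the precision of baseline adjustment. Simulations at 264 vs 88 on that assumption gave power of about 77 to 80% with balanced groups, but about 62 to 65% when the baseline outcome strongly drove group membership. This stands as a limit: 468 and 68% belong to the unweighted contrast. It does not establish the printed 80%, because the sizing paragraph does not mention weighting, and the article states weighting only under Aim 1 and lists no propensity covariates.

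**Stronger readings to avoid.** A reader might infer that weighting must lower power below 68%. The simulations show that it can move power either way, and the article gives nothing from which to fix the size. A reader might also infer that enrolment should rise to 468/0.8 = 585. That follows only if the unweighted change-score contrast is kept and 80% power at 0.3 SD is insisted on; the documents do not force either.

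**Conclusion.** Wrong as written. The 80% power claim is not a property of the analysis that the section names. For an unweighted change-score difference-in-differences with the article's own inputs, 468 evaluable participants are needed rather than 352. Power at 264 vs 88 is about 68%, and the effect detectable with 80% power is 0.345 SD rather than 0.30 SD. A one-sided test narrows the gap (368 needed, 78.6% power) but does not reproduce 352.

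The conclusion rests on the stated ρ = 0.5, equal variances at the two time points, and a two-sided 5% test. It leaves out weighting and crossover between groups, as the printed calculation also appears to do. It does not show that the study is too small for every analysis the text allows: a baseline-adjusted regression has 80.4% power at 264 vs 88 before weighting.

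**What to change.** Choose one of two wordings, before 12-month results are known:

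1. Keep difference-in-differences and restate the Aim 2 power at 264 vs 88: about 68% for 0.3 SD, or 80% for 0.345 SD.
2. Name regression of the 12-month outcome adjusted for its baseline value as the Aim 2 analysis, in both Power and Sample Size and Aim 2. Then 352 stands before any effect of weighting. Because the groups are not randomised, give the reason for preferring this contrast to a comparison of changes.

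In either case, say whether the test is two-sided, and state that the calculation does not include inverse-probability weighting, whose effect on power depends on the propensity model and on the imbalance between groups.

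The cost is a few sentences in the article and the analysis plan, with no change to enrolment or conduct. Under the first option the stated power becomes less favourable. Under the second the named Aim 2 analysis changes, and with it possibly the quantity estimated.

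### The model named for the baseline/12-month outcomes has no stated baseline term, yet the stated 352 gives 80% power only with baseline adjustment; difference-in-differences has about 68%

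*Protocol article*

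**What the plan says.** The Power and Sample Size section covers Aims 1 and 2 together, "for which statistical analysis will use a “difference-in-differences” approach". The contrast that fixes the total is the two-visit one: "Power was calculated to ensure the detection of differences between the baseline and 12-month follow-up survey in Aim 2". Its inputs are given as "Assuming a 3:1 ratio of MM versus comparison group and within-subject correlation of variables of 0.5", with a target of 0.3 SD between groups and, as the example outcome, "eg, reduction in pain intensity measured by GCPS". The result is stated "with 80% power (type I error=0.05), is 352 (264 vs 88"), raised to 440 (330 vs 110) for 20% attrition. Table 2 shows that GCPS is collected only at baseline and 12 months.

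The Aim 2 section then splits the data in two. For the first type, "For intensive longitudinal data, separate GLMM or GEE models will be built to compare longitudinal trajectories in each outcome". For the second, which takes in the core survey, cognitive tests and telomere length, "For measures collected only at baseline and 12 months, generalized linear regression models will be used to compare group differences in the survey data". That second sentence does not say whether the response is the 12-month value or the change, and it mentions no baseline covariate. The Abstract's methods paragraph lists only mixed models and generalized estimating equations for short- and long-term effects.

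**The concern.** The sample size rests on the correlation between a person's two measurements. That correlation helps only if the analysis uses the baseline value, and how much it helps depends on how the baseline is used. Entering it as a covariate, subtracting it to form a change, and leaving it out give different precision. The sizing section names one approach (difference-in-differences), the Aim 2 sentence names a model family that fits several, and the stated number may match only one of them.

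Two things are at stake. One is whether the study has the power it claims on the outcome type that sized it. The other is bias: under Group Assignment, participants join a group by their own interest in starting medical marijuana (MM), so baseline differences are likely. An analysis of 12-month values alone would pass those differences into the estimated effect.

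**Working it through.** **Inputs** (Power and Sample Size): 264 vs 88 evaluable; difference d = 0.3 SD; within-subject correlation r = 0.5; type I error 0.05; power 80%. Assumptions: the test is two-sided (not stated), SD is the cross-sectional SD, and it is equal at both visits.

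**Step 1: reproduce the 352.** With 3:1 allocation, the comparison group needs n = (1 + 1/3) × (1.960 + 0.842)² × V / d², where V is the variance factor. This is 1.333 × 7.849 × V / 0.09 = 116.3 × V.

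- 12-month value adjusted for baseline: V = 1 − r² = 0.75, so n = 87.2, rounded up to 88. Total 88 + 264 = **352**, and 352/0.8 = **440**. Both stated figures are reproduced exactly.
- Change score (difference-in-differences): V = 2(1 − r) = 1.0, so n = 117. Total 117 + 351 = 468, or 468/0.8 = 585 enrolled.
- 12-month value alone: V = 1.0, so again 468 and 585.

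A one-sided test does not rescue the other forms. They would need 368, and the baseline-adjusted form would need 276.

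**Step 2: power at 264 vs 88.** Let k = √(1/264 + 1/88) = 0.1231. The standard error is k√V, and power is Φ(0.3/SE − 1.960), with a negligible other tail.

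| Analysis | SE | Power | Simulated power (4,000 runs) | Simulated type I error |
|---|---|---|---|---|
| 12-month value, baseline as covariate | 0.1231 × √0.75 = 0.1066 | 80.4% | 79.8% | 4.7% |
| Change score / paired difference-in-differences | 0.1231 × √1 = 0.1231 | 68.3% | 68.6% | 5.2% |
| 12-month value alone | 0.1231 | 68.3% | 67.8% | 4.8% |

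With the change score, the difference detectable at 80% power is 2.802 × 0.1231 = 0.345 SD, not 0.3.

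**Step 3: where the loss comes from.** At r = 0.5, 2(1 − r) = 1. A properly paired change score is therefore exactly as precise as the 12-month value alone. The gap between 80% and 68% comes from leaving the baseline out as a covariate, not from failing to pair the visits.

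**Step 4: dependence on r.** Power at 264 vs 88:

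| r | Change score | Baseline as covariate |
|---|---|---|
| 0.3 | 54.0% | 72.4% |
| 0.5 | 68.3% | 80.4% |
| 0.625 | 80.4% | 87.7% |
| 0.8 | 97.1% | 98.2% |

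The change score reaches the stated 80% at r of about 0.625, where 2(1 − r) = 0.75. The 12-month value alone stays at 68.3% for every r.

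**Step 5: baseline differences (illustration; the documents give no figure).** Assume no MM effect and a 0.2 SD gap at baseline, with no adjustment or weighting. If half the gap remains at 12 months, the 12-month-only comparison is shifted by 0.1/0.1231 = 0.81 standard errors and rejects in about 13% of studies. If all of it remains, the shift is 0.2/0.1231 = 1.62 and it rejects in about 37%.

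**The case against.** The best defence is that the Aim 2 sentence is brief rather than wrong. Generalized linear regression can take the change as its response or the baseline as a covariate. Either uses one row per person and gives valid standard errors with no participant term. The sizing section speaks of differences between baseline and 12 months and of a reduction in pain, so baseline is clearly meant to be used somehow. The exact match of 352 to the baseline-adjusted formula suggests that such a regression may be what was intended. An article may leave covariate lists to an analysis plan. For baseline imbalance, Aim 1 provides propensity-score weighting, although the Aim 2 text does not expressly carry it over to the two-visit outcomes.

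Much of this stands. A reader might infer, because mixed models and GEE are assigned only to the intensive data, that the two visits will be stacked as independent records and the pairing lost. The documents describe no such analysis, and the declared difference-in-differences approach fits an ordinary regression of change scores, which keeps the pairing. That inference should not be drawn.

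The conflict with the stated power is not removed. The article commits to a number that depends on a term it does not name. The approach it does name, correctly carried out, falls short of that number at the article's own correlation.

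**Conclusion.** The point holds as a mismatch between the declared contrast, the named model and the stated power. Of the three forms compared, only the 12-month value adjusted for its baseline gives 80% at 264 vs 88 (80.4%), and neither the sizing section nor Aim 2 names it. The declared difference-in-differences has 68.3%, about 12 percentage points less. Comparing 12-month values alone also has 68.3% and is open to baseline differences between self-selected groups, though nothing says this form will be chosen.

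The figures rest on r = 0.5, a two-sided test and equal SDs at the two visits. At r = 0.5 the SD of the change equals the cross-sectional SD, so reading 0.3 SD either way leaves the difference-in-differences figure unchanged. If inverse probability weighting is also applied here, it would lower all these powers further; the documents give no basis for saying by how much. The false-positive figures in step 5 are illustrative only.

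**What to change.** In the Aim 2 section, replace the model sentence for two-visit measures with wording such as: *For measures collected only at baseline and 12 months, the 12-month value will be regressed on group and the baseline value of the same measure, with robust standard errors. The difference-in-differences estimate (change score, or group, visit and group-by-visit terms by GEE clustered on participant) will be reported alongside.* This matches the 352 and uses data and model families already planned.

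In Power and Sample Size, say that the 352 refers to the baseline-adjusted analysis. If difference-in-differences is kept as the main contrast, restate its power there as about 68% at r = 0.5; 80% would need 468 evaluable, 585 enrolled. Bring the Abstract's list of models into line.

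The cost is wording, with no new data or participants. The small downside is that in non-randomised groups the two estimates can differ when baselines differ, which is why both should be shown. The Results section says that data analysis is under way, so the choice of main estimate should be fixed and dated before group results are seen.
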